# Fully constrained acetabular liner vs. dual mobility hip joint in the surgical treatment of metastatic bone disease of the hip: study protocol for a randomized, open-label, two-arm, non-inferiority trial evaluating the post-operative hip dislocation rate

**DOI:** 10.1186/s13063-023-07237-9

**Published:** 2023-03-18

**Keywords:** Metastatic cancer, Pathologic fracture, Total hip arthroplasty, Constrained liner, Dual mobility

## Abstract

**Background:**

Patients receiving total hip arthroplasty (THA) due to metastatic bone disease of the hip (MBD) are at an increased risk of post-operative joint dislocation compared to other populations. Different joint solutions have been developed with the purpose of reducing the dislocation risk compared to regular THAs. One of these solutions, the constrained liner (CL), has been used increasingly at our department in recent years. This design, however, is prone to polyethylene wear and higher revision rates. An alternative is the dual mobility cup (DM), which has been shown to reduce the risk of dislocation in other high-risk populations. Few studies have investigated DM for THA due to MBD, and no studies have directly compared these two treatments in this population. We therefore decided to conduct a trial to investigate whether DM is non-inferior to CL regarding the post-operative joint dislocation risk in patients receiving THA due to MBD.

**Materials and methods:**

This study is a single-center, randomized, open-label, two-arm, non-inferiority trial. We will include 146 patients with MBD of the hip who are planned for THA at the Department of Orthopedic Surgery, Rigshospitalet. Patients with previous osteosynthesis or endoprosthetic surgery of the afflicted hip, or who are planned to receive partial pelvic reconstruction or total femoral replacement, will be excluded. Patients will be stratified by whether subtrochanteric bone resection will be performed and allocated to either CL or DM in a 1:1 ratio. The primary outcome is the 6 months post-operative joint dislocation rate. Secondary outcomes include overall survival, implant survival, the rate of other surgical- and post-operative complications, and quality of life and functional outcome scores.

**Discussion:**

This study is designed to investigate whether DM is non-inferior to CL regarding the risk of post-operative dislocation in patients receiving THA due to MBD. To our knowledge, this trial is the first of its kind. Knowledge gained from this trial will help guide surgeons in choosing a joint solution that minimizes the risk of dislocation and, ultimately, reduces the need for repeat surgeries in this patient population.

**Trial registration:**

ClinicalTrials.gov Identifier: NCT05461313. Registered on July 15 2022. This trial is reported according to the items in the WHO Trial Registration Data Set (Version 1.3.1).

## Background

The hip is the most frequent surgery-requiring site for metastatic bone disease (MBD) of the extremities [1]. Once disseminated, the metastatic lesions drive an osteolytic cascade, causing pain and affecting limb function [2]. In some patients, pain and local progression of the osteolytic lesion can be managed with radiotherapy or bone conserving treatments such as bisphosphonates [2]. However, some patients experience a progression into a pathologic fracture or an impending fracture despite relevant treatment, while others present with a pathological fracture as the first sign of metastatic disease. In these patients, surgery is warranted with total hip arthroplasty (THA) as the treatment of choice [3].

Total hip arthroplasty is one of the most successful operations within orthopedic surgery and provides many patients with a pain-free and well-functioning hip [4]. According to the Danish Hip Arthroplasty Register, a registry that has collected data since 1995, complications seen after THA are relatively few with the most common causes for all-time implant revision being aseptic loosening and dislocation [5]. A recent Danish register-based study found a 2-year cumulative incidence of dislocations of 3.5% after primary THA due to osteoarthritis, with 75% of dislocations occurring within the first 3 months after surgery [6]. Some populations though, such as patients with MBD, have a higher risk, with hip dislocation rates reported between 7 and 13% [7–9]. A record review of patients treated in our institution showed that 88% of dislocations occurred within the first 6 post-operative months. The dislocation itself is a very painful and devastating experience for the patient and requires hospital readmission with joint reduction performed under general anesthesia in the operating theater. Since the purpose of THA in MBD is not curative but rather to alleviate pain and preserve limb function, and given that the 1-year survival following surgery is approximately 40% [1, 10, 11], it is crucial to select a treatment that minimizes the risk for hospital readmission and avoids repeat surgery. Different articulations have been developed to mitigate the risk of joint dislocation compared to a regular THA. For example, constrained acetabular liners (CL) are used in revision surgeries for patients with repeated dislocations and in other high risk populations [12]. This option has been used increasingly in our department in the past years in patients with MBD. However, constrained liners are prone to polyethylene wear and high revision rates in the long run [13, 14], while the constrained design potentially impedes the patient with a restricted range of joint motion [15]. An alternative to the constrained liner is the dual mobility cup (DM), which has been shown to decrease the risk of dislocation in other high-risk populations such as revision THA patients and hip fracture patients [16–18]. The dual mobility design also provides an added benefit of a less restricted range of motion [19], which potentially could translate to better functional outcomes in everyday life. To date, few studies have evaluated dual mobility cups in patients with MBD, and no study has directly compared these two treatment options in this population. Given that dual mobility cups are proposed to be associated with fewer complications than constrained liners, we want to investigate whether these constitute a viable alternative in patients with MBD. The purpose of this trial is therefore to investigate if dual mobility cups are non-inferior to constrained liners regarding the post-operative dislocation risk in patients with MBD.

## Methods and design

### Study design and objectives

The current study is investigator initiated and designed as a randomized, two-arm, open-label non-inferiority study. The study is a single-center study performed at the Musculoskeletal Tumor Section at the Department of Orthopedic Surgery, Rigshospitalet, Denmark. Patients will be stratified by whether subtrochanteric bone resection is performed and randomly allocated to either CL or DM in a 1:1 ratio. The primary objective is to assess whether DM is non-inferior to CL regarding the post-operative joint dislocation risk. Secondary objectives include the overall survival, implant survival, the post-surgery complication rate, investigator reported outcomes, and patient reported outcomes (see the “ Outcome measures” section).

### Eligibility criteria

We will include patient that meet the following criteria: ≥ 18 years of age, diagnosed with metastatic bone disease of the hip (defined as bone lesions in the proximal femur and/or acetabulum because of a secondary malignant growth of a primary cancer located elsewhere or due to hematological malignancies), determined eligible for THA by a multidisciplinary board of physicians and surgeons. Patients will be excluded if they have previously had an osteosynthesis or endoprosthetic surgery of the ipsilateral hip, are planned to receive partial pelvic reconstruction or total femoral replacement, have previously been enrolled in the study, are unable to provide informed consent, or if it is not surgically viable to insert the acetabular and/or femoral component. In the case of patients referred for bilateral surgery, only the first surgery will be included.

### Enrollment

The Department of Orthopedic Surgery, Rigshospitalet, is a highly specialized tertiary center that maintains one of two dedicated units for orthopedic oncology in Denmark. The musculoskeletal tumor section at Rigshospitalet thus services an intake area that covers three of Denmark’s five regions (Capital Region and Regions of Zealand and Southern Denmark). Patients will be recruited among patients referred to the clinic for surgical treatment of MBD of the hip. Upon receiving the referral, a multidisciplinary board of physicians and surgeons review each case and assess whether surgical intervention is warranted. Subsequently, patients will be recruited among all patients approved for THA due to MBD of the hip. Following approval, a research staff will screen patients for eligibility. Upon arrival to the study site, eligible patients will be informed about the existence of the project by the treating staff. The treating staff will ask if the patient is interested in further information from the research staff. If verbal consent is obtained, a person from the research staff will reach out to the patient and provide thorough oral and written information. An adequate reflection period will be provided before written consent is obtained and any study related procedures are commenced.

### Surgical procedure

All patients in this study will undergo THA with the insertion of an artificial hip joint due to MBD. All surgeries will be performed by attending surgeons specialized in orthopedic surgery with experience with orthopedic oncology, ensuring an adequate skillset and routine in the procedures. All surgeries will be performed using the posterior approach and with cementation of both the acetabular and femoral components. The acetabular components in this study will either be a constrained liner or a dual mobility cup. The constrained liner used in this study will either be a Freedom Constrained Acetabular Liner or G7 Freedom Constrained Acetabular Liner (Zimmer Biomet). The dual mobility cup used in this study will be the Avantage™ Acetabular System (Zimmer Biomet).

### Follow-up and end of study

Follow-up will be performed on post-operative months 3, 6, 12, and 24. The follow-ups will include a record review of the electronic patient record, an evaluation at the outpatient clinic, and patient-reported questionnaires. The following variables will be obtained and stored in a REDCap database:Date of primary completion or study withdrawalReason for study withdrawal (if relevant)Implant data (type, femoral head diameter, stem diameter, stem length)Surgical data (“knife to skin” time, blood loss)Post-operative complications (type, date, action taken)Length of hospital stay (days)Joint dislocation (date, action taken)Complications other than joint dislocation (type, date, action taken)Hospital readmission (reason, date)Karnofsky Performance Status Score [20] after 3, 6, 12, and 24 months post-operativelyMusculoskeletal Tumor Society Score (MSTS) [21] after 3, 6, 12, and 24 months post-operativelyHarris Hip Score (HHS) [22] after 3, 6, 12, and 24 months post-operativelyEuropean Quality of Life—5 Dimensions Questionnaire (Eq-5d) [23] score after 3, 6, 12, and 24 months post-operativelyToronto Extremities Salvage Score (TESS) [24] after 3, 6, 12, and 24 months post-operatively

### Study withdrawal and replacement

Patients have the right to withdraw from the study at any time and for any reason without prejudice to their future medical care by the physician or at the institution. Patients can decline to continue in any protocol-required procedures at any time during the study. Furthermore, the investigator can decide to withdraw a patient from the study at any time prior to study completion for the reasons listed below:In-surgery decision to either diverge from the allocated treatment, perform partial pelvic reconstruction, or insert a total femoral replacementLoss to follow-up or migrationRevision surgery of the ipsilateral hip

Patient data up to the withdrawal of the patient will be included in the study. We will record the date and reason for withdrawal. Where permitted, available data can be included after withdrawal of consent. We do not expect loss to follow-up regarding the primary outcome due to the organization of the Danish healthcare system. Healthcare in Denmark is public and taxpayer funded. All hospital contacts are documented in the electronic patient record and stored in the digital health record (Danish: *Sundhedsjournalen*). As hip dislocations are always treated in a hospital setting in Denmark, we expect this information to be available for all patients. In case that a patient is withdrawn prior to completion of the surgery (i.e. before wound-closure is completed), a new patient will be enrolled and randomized until the study includes a minimum of 73 patients that complete the surgery in each of the treatment arms (see the “ Sample size calculation” section).

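### Withdrawal at revision of the study hip, with data provided for only up to withdrawal, permits outcome-dependent loss of follow-up and conflicts with the plan's own analysis populations

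*Protocol article*

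**What the plan says.** All references are to the protocol article.

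*Study withdrawal and replacement* gives the investigator discretion: "the investigator can decide to withdraw a patient from the study at any time prior to study completion for the reasons listed below". One of the listed reasons is revision of the ipsilateral hip. The data rule follows: "Patient data up to the withdrawal of the patient will be included in the study". The next provision on later data is "Where permitted, available data can be included after withdrawal of consent". The section then says "We do not expect loss to follow-up regarding the primary outcome due to the organization of the Danish healthcare system", and on ascertainment: "As hip dislocations are always treated in a hospital setting in Denmark, we expect this information to be available for all patients".

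Other sections bear on this:
- *Secondary outcomes* lists dislocation at further time points, implant survival, overall survival and complications. It defines the Karnofsky, MSTS, HHS, EQ-5D and TESS comparisons in patients alive at each time point, without excluding revised patients.
- *Data analysis* promises both a per-protocol and an intention-to-treat analysis.
- *Follow-up and end of study* schedules record review, clinic evaluation and questionnaires at months 3, 6, 12 and 24.
- *Background* says that "constrained liners are prone to polyethylene wear and high revision rates in the long run" and that "dual mobility cups are proposed to be associated with fewer complications than constrained liners".

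**The concern.** Revision happens after randomisation and is caused in part by the implant; it bears directly on one of the trial's own secondary outcomes, implant survival. If follow-up may end there, attrition depends on outcome. The decision rests with an investigator who can know the allocation, because the trial is open-label. Blinding the data analysis does not repair this, since the loss occurs before analysis.

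The function and quality-of-life scores are most exposed. They need continued visits and questionnaires, and the reassurance about hospital records does not cover them. A score that was never collected cannot be recovered by any later analysis plan. Later complications, and vital status for overall survival, may also be cut short if record review ends with withdrawal.

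For dislocation, two statements in one section pull apart: data up to withdrawal, and information expected for all patients. The primary conclusion turns on very few events, so the text should settle which applies.

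**Working it through.** **1. The statements side by side.** A patient revised at, say, month 4 and withdrawn by the investigator has not withdrawn consent. The data-up-to-withdrawal rule applies, and the exception does not by its wording. If alive at months 6, 12 and 24, the same patient belongs to the function populations in *Secondary outcomes* and to the intention-to-treat analysis in *Data analysis*. Both cannot be honoured for scores once visits stop. For dislocation, the hospital-record sentence suggests that the information would still exist; the data rule does not say that it would be used.

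**2. The plan's own sample size.** Inputs from *Sample size calculation*: event risks 0.01 (CL) and 0.02 (DM), margin 0.06, one-sided 5% level, power 80%.

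n per arm = [0.01×0.99 + 0.02×0.98] × (1.645 + 0.842)² / (0.06 − 0.01)² = 72.95, rounded up to 73. The stated figure is reproduced. It contains no allowance for patients withdrawn after surgery. With 2, 4 or 7 patients per arm not evaluable (71, 69 or 66 left), power falls from 80.0% to 79.0%, 78.0% or 76.4%.

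**3. How few events decide the primary outcome.** One patient is 1/73 = 1.37 percentage points. One-sided 95% upper bound, using the simple normal (Wald) interval as an assumption because the article does not name the interval method:

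UB = (d − c)/73 + 1.645 × √[p_CL(1 − p_CL)/73 + p_DM(1 − p_DM)/73], with c CL events and d DM events.

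| CL events | UB at 2 DM events | UB at 3 DM events |
|---|---|---|
| 0 | 5.88% | 7.93% |
| 1 | 5.23% | 7.17% |
| 2 | 4.44% | 6.32% |

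In each row, two DM events meet the 6% margin and three do not. One uncounted DM dislocation could therefore turn a failure into a success.

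**4. How many dislocations might go uncounted.** No figure is given, so this is assumption only. If 5% of an arm were revised for reasons other than dislocation (73 × 0.05 = 3.65 patients), and 13% of these later dislocated (the top of the 7–13% range in *Background*), 3.65 × 0.13 = 0.47 events per arm would be at risk. At the plan's own 1–2%, it is 0.04 to 0.07. A dislocation that itself leads to revision precedes withdrawal and is counted.

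**5. Function scores.** Assume that unrevised patients have the same mean in both arms and that revised patients score D points lower on a 0–100 scale. With revised shares r_CL and r_DM among those scored, the true DM − CL difference is (r_CL − r_DM) × D. Dropping revised patients sets it to zero, so that product is the bias.

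| r_CL / r_DM | D = 10 | D = 20 | D = 30 |
|---|---|---|---|
| 5% / 5% | 0 | 0 | 0 |
| 5% / 2% | 0.3 | 0.6 | 0.9 |
| 10% / 5% | 0.5 | 1.0 | 1.5 |
| 10% / 2% | 0.8 | 1.6 | 2.4 |
| 15% / 5% | 1.0 | 2.0 | 3.0 |

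The range is 0 to 3 points over these pairs. The more extreme pair of 15% and 2% with D = 30 would give 0.13 × 30 = 3.9. If DM were revised more often, the sign would reverse. With about 40% alive at one year (*Background*), 0.40 × 73 = 29.2 patients per arm remain, so each revised survivor is about 1/29.2 = 3.4% of an arm's 12-month comparison.

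**The case against.** The strongest reply is that the text does not say what a quick reader might infer, namely that data on revised patients always stop.

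- **Withdrawal is permitted, not required.** The text commits to using earlier data and does not expressly discard later data. It would also be odd to allow data after consent is withdrawn yet bar them when consent stands. This stands as a possible reading, but no sentence provides for it.
- **Dislocations after revision are not shown to be lost.** The section expects record information on all patients, and record review is part of follow-up. This stands: the defect is an unresolved inconsistency, not a certain loss of primary events. The 0.47 figure also uses the top of a cited range and is assumed equal in both arms, so it would largely cancel in a risk difference.
- **The rule does not hide the main disadvantage expected of CL.** That disadvantage is revision itself. The event counts in implant survival, and the reason for withdrawal is recorded. This stands.
- **Function and survival would not be compared only in patients with intact implants.** Data before withdrawal remain. Overall survival suffers only if vital status is no longer collected, which the text leaves open.
- **Unequal loss by arm is not established.** The statement about CL revisions concerns the long run, follow-up is 24 months, and no arm-specific rate is given. With equal rates, the bias in the function model is zero.
- **The function shift is small against sampling error.** With an assumed SD of 20 and 29 per arm, the standard error of the difference is 20 × √(2/29) ≈ 5 points.

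Detailed handling of data after withdrawal could also sit in an analysis plan or full protocol that is not shown. That does not answer the point about scores: whether they are collected depends on who stays in follow-up, which this section governs.

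**Conclusion.** The point holds as a defect in the withdrawal rule. As written, the rule permits discretionary attrition that depends on a treatment-related outcome, in an open-label trial, and possibly unequally by arm. It conflicts with the intention-to-treat commitment and with function populations defined by survival alone. Later function and quality-of-life scores are the clearest loss. Later complications and vital status may be affected, and the section is inconsistent on dislocation.

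The size of the bias cannot be computed, because the article gives neither a revision rate by arm nor a score deficit after revision. Under the assumed pairs, the mean function difference moves by about 0 to 3 points. For the primary outcome, the figures show only that one DM event can change the conclusion (5.23% against 7.17% with one CL event, under a Wald bound). They do not show that such an event would be lost. Readings under which post-revision data certainly vanish, or CL's failures are concealed, go beyond the text.

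**What to change.** In *Study withdrawal and replacement*:
1. Delete revision of the ipsilateral hip as a reason for study withdrawal, and record it as an outcome with date and reason.
2. State that revision ends neither follow-up nor inclusion in the intention-to-treat analysis. Record review, visits and questionnaires continue to month 24 in the allocated arm.
3. Count dislocations after revision, within 6 months of the index surgery, in the intention-to-treat primary analysis, and add a sensitivity analysis that stops at revision.
4. Reconcile the data-up-to-withdrawal sentence with the expectation of complete dislocation information, with the survivor populations in *Secondary outcomes*, and with *Data analysis*.

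The sample size stays at 73 per arm. The cost is a wording amendment and continued follow-up of a few revised patients at visits already scheduled. *Trial status* reports that recruitment has begun, so the change should be made soon: scores missed in the meantime cannot be collected afterwards.

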### Outcome measures

#### Primary outcome

The 6-months hip dislocation rate in patients receiving a dual mobility cup compared to patients receiving a constrained liner for the surgical treatment of MBD

#### Secondary outcomes

The 3-month, 1-year, and 2-year hip dislocation rate in patients receiving a dual mobility cup compared to patients receiving a constrained liner for the surgical treatment of MBDThe 3-months 6-month, 1-year, and 2-year implant survival in patients receiving a dual mobility cup compared to patients receiving a constrained liner for the surgical treatment of MBDThe 3-month, 6-month, 1-year, and 2-year overall survival in patients receiving a dual mobility cup compared to patients receiving a constrained liner for the surgical treatment of MBDThe incidence of post-surgical and prosthesis-related complications in patients receiving a dual mobility cup compared to patients receiving a constrained liner for the surgical treatment of MBD. These include but are not limited to deep venous thrombosis, pulmonary embolism, wound infections, periprosthetic infections, periprosthetic fractures, etc.The 3-month, 6-month, 1-year, and 2-year Karnofsky Performance Status Score in patients receiving a dual mobility cup compared to patients receiving a constrained liner for the surgical treatment of MBD and that are alive at the defined time pointThe 3-month, 6-month, 1-year, and 2-year MSTS in patients receiving a dual mobility cup compared to patients receiving a constrained liner for the surgical treatment of MBD and that are alive at the defined time pointThe 3-month, 6-month, 1-year, and 2-year HHS in patients receiving a dual mobility cup compared to patients receiving a constrained liner for the surgical treatment of MBD and that are alive at the defined time pointThe 3-month, 6-month, 1-year, and 2-year Eq-5d score in patients receiving a dual mobility cup compared to patients receiving a constrained liner for the surgical treatment of MBD and that are alive at the defined time pointThe 3-month, 6-month, 1-year, and 2-year TESS in patients receiving a dual mobility cup compared to patients receiving a constrained liner for the surgical treatment of MBD and that are alive at the defined time point

